### Sample size

As our primary outcomes are feasibility it is desirable to keep the sample size small enough to allow close monitoring of participants and the programme while large enough to obtain sufficient data on our primary outcomes of feasibility. For feasibility reasons we will ensure we have sufficient numbers in each group to generate a ‘group’ climate likely to maximise adherence. Hence if the group gets too small, it becomes unviable for participant engagement and sense of community. The minimum numbers required to sustain a community-based music and movement programme and maintain the required group dynamics is between 10–12 older adults per group; guided by practice expertise within the research team and previous feasibility studies (
Clifford *et al.*, 2021;
O’Regan *et al.*, 2020). The primary feasibility outcomes will be evaluated by assessing recruitment rates (the rate of participants recruited to the study); retention rate (the number of participants who complete measures at baseline and at follow up post intervention) and minimum average attendance (number of participants who attended at least 65% of the intervention sessions). Hence, we aim to recruit a minimum of 72 participants in total (n=12 per cluster) allowing for 20% attrition (n=60; n=10 per cluster), we will be able to estimate a recruitment rate of 60% within a 95% confidence interval +/- 12.6%; a retention rate of 80% within a 95% confidence interval of +/- 10.3% and a minimum average attendance of 65% within a 95% confidence interval of +/- 12.3%. 

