### Randomisation

Pragmatic randomised controlled trials (RCTs) are conducted to answer the important question of how an intervention works in real-world contexts in a heterogeneous real-world population. Thus, we plan to recruit individuals in the Mid-West of Ireland from at least six geographical regions or clusters; the groups of study participants are the units of randomisation (clusters), and individuals within these groups are the units of analysis. The clusters are based on the geographical regions where the participants reside (two clusters in each county n=6 geographical regions, with n=2 additional reserve clusters sites). Using block randomisation, the clusters will be randomised to either the intervention or control (usual care) using 1:1 allocation ratio. Thus, there will be an intervention and a control group in each county. Given the wide geographical spread of these locations, it would be impractical to conduct an RCT by randomising participants individually to either the intervention or control arm and then find a central location to conduct the intervention. Additionally, this approach would not keep the community groups together. The cluster RCT design will ensure we keep community groups together. Research from a recent cluster-randomised controlled study, demonstrated that being ‘
*part of a local community group*’ can afford additional benefits, including an increased likelihood to remain active due to the friendships they had formed (OR=3.04, 95% CI=1.65–5.60, p=0.001), as a result of attending of the programme (
O'Regan *et al.*, 2021). In line with our pragmatic approach the study will have two phases for recruitment and two implementation blocks as the intervention can apply naturally to the group. Participants in the same group will receive the same intervention, thus approximating clinical practice, and producing generalisable findings.

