Recruitment rates: will be assessed by reporting the recruitment rate (as the number of participants recruited and randomised per centre per month and the number of people enrolled over the number of people who expressed an interest in taking part). Refusal rates will also be documented where provided.Retention: proportion of individuals who after enrolment completed the baseline and follow-up assessments. We will record numbers who completed baseline and assessment at 12-week follow-up and attendance at programme. We will calculate the minimum outcome assessment target, which is set at a retention rate of at least 80% of recruited participants with valid baseline and 12-week primary outcome data i.e., less than 20% attrition at outcome assessments at baseline and follow-up.Attendance at supervised sessions: We will record the percentage of participants that attend the supervised sessions (adherence). Minimum average attendance target will be determined as the minimum average attendance by recruited participants set as 65%.Participation in home exercise programme: Using a self-complete calendar we will record how many participants (and how often) they engage in the home exercise programme.Safety will be assessed through self-report of direct or unrelated adverse events (e.g., falls or pain during the programme period). Falls: A falls diary (Appendix 7) will be completed. Participants or a nominated family member/career will receive a weekly reminder to complete the log. Completing a falls diary encourages recall, identifies the key circumstances surrounding falls and their content focuses the programme. The falls diary will include: Date and time of fall; location of fall; what caused the fall; type of injury sustained; and action taken. The falls diary is more accurate than retrospective recall over varying time periods.

The variability, consistency, response rates and data completeness for each of the secondary outcome measures will be determined. The secondary outcomes of the study have been used in previous studies with older adults, have undergone psychometric testing and include:

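### The ±12.3% precision stated for attendance pools both arms; only the programme arm (36 people at the planned minimum) can attend sessions, so the margin is about ±15.6% before clustering

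*Protocol article*

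**What the plan says.** All of this is in the protocol article.

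- **Sample size** sets the target: "we aim to recruit a minimum of 72 participants in total (n=12 per cluster) allowing for 20% attrition (n=60; n=10 per cluster"). It then gives three expected precisions: ±12.6 points around 60% for recruitment, ±10.3 points around 80% for retention, and, for the third outcome, "a minimum average attendance of 65% within a 95% confidence interval of +/- 12.3" percentage points. It does not say which denominator was used. Attendance is defined there as the number of participants reaching at least 65% of the intervention sessions.
- **Randomisation** describes six geographical clusters, two per county, with two reserve sites, and says "the clusters will be randomised to either the intervention or control (usual care) using 1:1 allocation ratio".
- **Control group** describes usual care, with the programme offered for six weeks only once data collection is over.
- **Assessment procedures** gives the operational definitions. Recruitment is reported both as a count per centre per month and as "the number of people enrolled over the number of people who expressed an interest in taking part". Retention is a proportion of recruited participants. Attendance is an average among recruited participants, with a target of 65%.

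**The concern.** A margin of error depends on how many people can contribute to the proportion. The three outcomes have three different populations: people who expressed interest (recruitment), people enrolled (retention) and people enrolled in a programme cluster (attendance). Yet the printed margins behave as if all three were measured in the same pooled group.

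For attendance this matters. It is a primary feasibility outcome, and of the three it is the only one specific to the programme. If half the trial cannot contribute to it, the stated precision is better than the design can deliver. A reader judging whether an observed 65% supports a definitive trial would then have too narrow an interval in mind.

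**Working it through.** **Inputs.** Recruited 72, 12 per cluster, 60 after attrition, and proportions 60%, 80% and 65% (Sample size). Six clusters allocated 1:1 (Randomisation). Recruitment and retention denominators (Assessment procedures). Confidence level 95%, z = 1.96.

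**Formula.** Half-width = 1.96 × √(p(1−p)/n), with no clustering term.

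**Step 1: reproduce the stated margins.** Solving for n = p(1−p) × (1.96/margin)²:

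- recruitment, 0.60 and 0.126: n = 58.1
- retention, 0.80 and 0.103: n = 57.9
- attendance, 0.65 and 0.123: n = 57.8

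Putting n = 58 back gives 12.61, 10.29 and 12.28, which round to all three printed figures. 72 × 0.80 = 57.6, so 58 is what 20% attrition from 72 leaves. The printed 60 is 60/72 = 83.3% of 72, an attrition of 16.7%. With the same formula, n = 60 gives 12.4, 10.1 and 12.1, which matches none of the three. A t-quantile with n = 60 gives 12.66, 10.33 and 12.32; this matches two of the three after rounding. On either reading, n is a pooled two-arm number after attrition.

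**Step 2: attendance on its own denominator.** Six clusters at 1:1 give three programme clusters: 3 × 12 = 36.

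- n = 36: 1.96 × √(0.65 × 0.35/36) = 1.96 × 0.0795 = 15.6 points. Interval 65 ± 15.6, about 49% to 81%, against 53% to 77% as stated.
- n = 30 (3 × 10, after attrition): 17.1 points.
- n = 48 (a fourth programme cluster of 12): 13.5 points.
- Reaching 12.3 points needs about 58 programme participants; 58/36 = 1.61, about 60% more than planned.

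**Step 3: clustering.** Design effect = 1 + (12 − 1) × ICC; the half-width is multiplied by its square root. The protocol gives no ICC, so these values are assumed.

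| Assumed ICC | Design effect | Attendance, n = 36 | Retention, n = 72 |
|---|---|---|---|
| 0 | 1.00 | ±15.6 | ±9.2 |
| 0.01 | 1.11 | ±16.4 | ±9.7 |
| 0.05 | 1.55 | ±19.4 | ±11.5 |
| 0.10 | 2.10 | ±22.6 | ±13.4 |

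**Step 4: the other two outcomes.**

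- Retention, 80% of 72 recruited: 1.96 × √(0.80 × 0.20/72) = 9.2 points, against 10.3 stated.
- Recruitment, as a proportion of those interested: if exactly 72 enrol at 60%, the denominator is 72/0.60 = 120, and 1.96 × √(0.60 × 0.40/120) = 8.8 points, against 12.6 stated.

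**The case against.** Several points on the other side are fair.

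- **The denominator is not printed.** The 58 is back-calculated, and so is the view that it means completers in both arms. This stands as a limit on how the point is worded. It does not rescue the attendance figure, because 58 and 60 both exceed the programme arm.
- **The size is not justified by precision alone.** A reader might infer that the sample size falls with these margins. It does not: the Sample size section first argues from the 10 to 12 people needed to sustain a group. The margins are the only statistical justification, not the only one.
- **All three margins might be thought too optimistic.** The documents do not support that. Before clustering, the retention and recruitment margins are wider than needed (10.3 against 9.2; 12.6 against 8.8). For retention this depends on ignoring clustering: in the table, 10.3 is too narrow once the assumed ICC is 0.05.
- **36 is a minimum.** The protocol speaks of at least six clusters and names two reserves. Using both, one per arm, gives 48 people and still ±13.5. One sentence under Concealed allocation could be read as two reserves in each arm, which would make 5 × 12 = 60 programme participants and ±12.1. But that section and Randomisation both count two reserves in total, and the margins are tied to a total of 72.
- **Attendance may be meant as an average.** Assessment procedures reads that way. Then neither 12.3 nor 15.6 applies, since the margin of a mean needs a standard deviation that the protocol does not give. Only programme participants would contribute in that case too.
- **No decision rule uses a confidence limit.** The retention and attendance targets are point values, so the error misstates precision but does not change a stated pass or fail.

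**Conclusion.** The attendance margin is wrong as written. At the planned minimum of 36 programme participants it is about ±15.6 points before clustering, not ±12.3: 15.6/12.3 = 1.27, so about 27% wider. Across the plausible programme-arm sizes of 30 to 48 it runs from ±17.1 to ±13.5, and at n = 36 clustering takes it to between ±16.4 and ±22.6 for assumed ICCs of 0.01 to 0.10. This rests on reading attendance as a proportion of participants, as the Sample size section does, and on the normal-approximation formula that reproduces the protocol's own figures.

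The retention and recruitment margins also use the wrong denominator, but they are secondary. Both are cautious before clustering. The recruitment replacement depends on an assumed 120 interested people, and a binomial margin has no meaning for the per-month count that the protocol also uses.

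**What to change.** Rewrite the precision sentence in the Sample size section so that each margin names its denominator.

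1. **Attendance:** 65% of all participants enrolled in programme clusters, drop-outs included, ±15.6% at n = 36. Add a range inflated by the square root of the design effect, with the ICC values stated as assumptions. Counting drop-outs agrees with the reference to recruited participants in Assessment procedures.
2. **Definition:** choose either the share of participants reaching 65% of sessions or the mean attendance, and use it in Sample size, Assessment procedures and Table 1. If the mean is chosen, replace the binomial margin with one based on a stated standard deviation.
3. **Retention (minor):** 80% of the 72 recruited, ±9.2% before clustering, with the same kind of inflated range.
4. **Recruitment (minor):** 60% of those expressing interest, about 120 if exactly 72 enrol, ±8.8%. Say that this margin does not apply to the count per centre per month.
5. **Attrition:** reconcile the printed 60 with 20% attrition from 72, which leaves about 58.

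The cost is wording and a less favourable attendance figure. No extra participants are needed unless ±12.3% is itself a requirement; that would take about 58 in the programme arm, ignoring clustering.

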### Randomisation

Pragmatic randomised controlled trials (RCTs) are conducted to answer the important question of how an intervention works in real-world contexts in a heterogeneous real-world population. Thus, we plan to recruit individuals in the Mid-West of Ireland from at least six geographical regions or clusters; the groups of study participants are the units of randomisation (clusters), and individuals within these groups are the units of analysis. The clusters are based on the geographical regions where the participants reside (two clusters in each county n=6 geographical regions, with n=2 additional reserve clusters sites). Using block randomisation, the clusters will be randomised to either the intervention or control (usual care) using 1:1 allocation ratio. Thus, there will be an intervention and a control group in each county. Given the wide geographical spread of these locations, it would be impractical to conduct an RCT by randomising participants individually to either the intervention or control arm and then find a central location to conduct the intervention. Additionally, this approach would not keep the community groups together. The cluster RCT design will ensure we keep community groups together. Research from a recent cluster-randomised controlled study, demonstrated that being ‘
*part of a local community group*’ can afford additional benefits, including an increased likelihood to remain active due to the friendships they had formed (OR=3.04, 95% CI=1.65–5.60, p=0.001), as a result of attending of the programme (
O'Regan *et al.*, 2021). In line with our pragmatic approach the study will have two phases for recruitment and two implementation blocks as the intervention can apply naturally to the group. Participants in the same group will receive the same intervention, thus approximating clinical practice, and producing generalisable findings.

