*Music and Movement for Health* programme. For the cost-utility analysis, Quality Adjusted Life-Years (QALYs) will be estimated using data collected via the EQ-5D-5L survey instrument at baseline and over the follow-up period. Missing data will be analysed to explore the validity of the data collection tools and the timing of their application. An incremental analysis will be conducted to calculate the mean differential in costs and QALYs between the control group and the programme group. The incremental cost-effectiveness ratio (ICER) will be calculated and analysed. Parametric and probabilistic analyses will be employed to explore uncertainty. The evidence generated from the pilot study will go to inform the design and conduct of a full economic evaluation to assess the cost-effectiveness of the developed programme.

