Table 1.

**Table 1. T1:** Summary of the key study objectives, outcomes and analysis plans.

Aim	Objectives	Outcome	Criterion for Feasibility	Statistical Analysis
**Primary**	Assess feasibility of recruitment, retention, group size and data completion.	Recruitment and retention rates, missing data.	*Music and Movement for Health* is feasible. The rate of participants recruited to the study, retention rate (the number of participants who complete measures at baseline and at follow up post intervention, minimum average attendance (number of participants who attended at least 65% of the intervention sessions). We will calculate the minimum outcome assessment target, as a retention rate of at least 80% of recruited participants with valid baseline and 12-week primary outcome data.	To assess if we can recruit and retain sufficient eligible older adults to inform a future definitive trial. Descriptive statistics: mean and SD for continuous variables proportions for dichotomous variables.
	Assess safety of the programme.	Safety: adverse effects e.g., falls, a weekly falls log will be completed.	The programme is safe. There is no increase in direct adverse events due to the intervention (e.g., falls during the intervention period).	Safety assessed through self-report of direct or unrelated adverse events (e.g., falls or pain during the programme period).
	To obtain participants’ & stakeholder feedback and experiences of the study processes and programme.	Qualitative study feedback.	*Music and Movement for Health* is acceptable. The majority of participants report that the study processes including measures were feasible and acceptable.	Thematic analysis. Data regarding combined completion and acceptability of measures.
	Objective	Outcomes	*Hypothesis*	Statistical Analysis
**Secondary**	To explore the differences between the groups for Physical Function, Balance, Physical Activity, Loneliness, Social Isolation, Mood, and Quality of Life.	Results for Clinical outcomes: Physical Function, Balance, Physical Activity, Loneliness, Social Isolation, Mood, and Quality of Life.	The programme group will show improvement in scales.	Regression analysis

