	To explore the differences between the groups for Physical Function, Balance, Physical Activity, Loneliness, Social Isolation, Mood, and Quality of Life.	Results for each outcome of interest.	We can determine the required sample size for a definitive trial.	ICC (intraclass correlation coefficient) will be used to calculate the design effect. Thus, the required sample size for a CRCT (cluster-randomised controlled trail) will be calculated by multiplying the required sample size for the equivalent ungrouped study with the DE.
	Pilot economic analysis to assess costs and inform a definitive trial.	A pilot economic analysis to inform the design and conduct of a full economic evaluation to assess the cost effectiveness of the programme developed.	The methods developed and implemented for the conduct of the pilot health economic analysis proved to be feasible and acceptable to study participants.	The criterion for success includes obtaining sufficient data on cost. Incremental analysis to calculate the mean differential in costs and QALYs. The incremental cost effectiveness ratio (ICER) will be calculated and analysed. Parametric and probabilistic analyses will be employed to explore uncertainty.

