### Data analysis

The quantitative data collected for this research will be input into IBM SPSS Statistics software package (version 27). As this is a feasibility study, the analysis will focus on descriptive statistics and confidence interval estimation. Continuous variables will be reported as means, standard deviation and 95% confidence intervals, and categorical data as the number and percentages. A content analysis will be performed on any data from open-ended questions. Qualitative data collected for this research will be analysed according to Braun and Clarke's 6-step framework for doing inductive thematic analysis, including familiarisation and theme generation, searching, reviewing and defining (
Braun & Clarke, 2019). Investigator triangulation will support integrity in the data analysis process. Thus, sample transcripts will be independently coded by members of the research team to discuss and agree on the codes and interpretations. The research team will meet to discuss the dataset and develop consensus around coding, interpretations, patterns, ideas and themes. NVivo software (London, United Kingdom) will be used to code and analyse the data using built-in functionality. The themes will be reviewed and discussed by all members of the research team to generate a thematic 'map' of the analysis.

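### Six clusters are randomised and individuals analysed, but no allowance for clustering is stated for this trial's intervals, and the sample-size margins assume independent observations

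*Protocol article*

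**What the plan says.** **Design.** The Randomisation section plans "two clusters in each county n=6 geographical regions, with n=2 additional reserve clusters sites", and "the clusters will be randomised to either the intervention or control (usual care) using 1:1 allocation ratio". It adds that each county will hold one intervention and one control group. So three clusters per arm are compared, paired by county. The same section states that "the groups of study participants are the units of randomisation (clusters), and individuals within these groups are the units of analysis".

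**Size and precision.** The Sample size section says "we aim to recruit a minimum of 72 participants in total (n=12 per cluster) allowing for 20% attrition (n=60; n=10 per cluster". It gives 95% margins of 12.6 points for a recruitment rate of 60%, 10.3 for retention of 80% and 12.3 for attendance of 65%.

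**Analysis.** The Data analysis section says "the analysis will focus on descriptive statistics and confidence interval estimation", with means, standard deviations and 95% confidence intervals for continuous variables. For the secondary between-group objective, Table 1 gives the hypothesis "The programme group will show improvement in scales" and names regression without saying which kind. The economic section says "An incremental analysis will be conducted to calculate the mean differential in costs and QALYs between the control group and the programme group", with unspecified parametric and probabilistic methods for uncertainty.

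**Clustering.** The only analytic use of the ICC is in Table 1: "ICC (intraclass correlation coefficient) will be used to calculate the design effect". That design effect multiplies the sample size of a definitive trial.

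**The concern.** People in one cluster share a locality, and in the intervention arm they also share sessions, facilitators and a programme tailored to their group. The Sample size section itself relies on a group climate to maintain adherence, and the Randomisation section cites friendships in local groups as a reason people stay active. Some similarity within clusters is therefore expected, both in outcomes and in retention and attendance.

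The authors recognise this for the next trial but state no allowance for it in this one. If none is made, two things go wrong. The variance is understated by the design effect, and the degrees of freedom are counted from about 60 people when only six units were randomised. The secondary aim is to obtain preliminary effect estimates, and the monitoring committee is to look at efficacy data. Intervals that look tighter than they are would mislead both uses. For the feasibility rates, the stated margins would promise more precision than the design can give.

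**Working it through.** **1. Reproduce the stated margins.** Half-width = 1.96 × √(p(1−p)/n × DE), with DE the design effect. Take DE = 1 and n = 58 (72 × 0.8 = 57.6, rounded up):

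| Rate | p | Computed | Stated |
|---|---|---|---|
| Recruitment | 0.60 | 12.61 | 12.6 |
| Retention | 0.80 | 10.29 | 10.3 |
| Attendance | 0.65 | 12.28 | 12.3 |

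All three match. Using the stated n = 60 gives 12.40, 10.12 and 12.07, and n = 72 gives 11.32, 9.24 and 11.02; neither matches. The stated margins are therefore independent-observation intervals.

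**2. Allow for clustering.** DE = 1 + (m−1) × ICC, with m = 10 per cluster and n = 60. The document gives no ICC, so 0.01 to 0.10 is assumed. The check applies the same n to all three rates, as the plan appears to do.

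| ICC | DE | Recruitment | Retention | Attendance |
|---|---|---|---|---|
| 0 | 1.00 | 12.4 | 10.1 | 12.1 |
| 0.01 | 1.09 | 12.9 | 10.6 | 12.6 |
| 0.05 | 1.45 | 14.9 | 12.2 | 14.5 |
| 0.10 | 1.90 | 17.1 | 14.0 | 16.6 |

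Example: 12.40 × √1.45 = 14.9. These still use 1.96 and make no correction for having few clusters.

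**3. Between-arm intervals if clustering is left out.** Normal outcomes with no true difference were simulated for three clusters per arm, and the arms compared with an ordinary individual-level t interval. The entries are the percentage of nominal 95% intervals that miss the true difference (target 5%).

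| Per cluster | Cluster variance between counties | ICC 0.01 | ICC 0.05 | ICC 0.10 |
|---|---|---|---|---|
| 12 | none | about 6 | about 12 | about 18 |
| 12 | half | about 5.5 | about 8 | about 11 |
| 10 | none | about 6 | about 10 | about 16 |
| 10 | half | about 5.5 | about 7.5 | about 10 |

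Variation between counties cancels because each county has a cluster in both arms. Only variation between clusters within a county harms the interval. At ICC 0 the ordinary interval covers 95%.

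**4. What a valid interval costs.** With 12 per cluster, an unpaired cluster-level interval on 6 − 2 = 4 degrees of freedom is wider than the ordinary one by √DE × t(4)/t(70). With m = 12, DE is 1.11, 1.55 and 2.10, which gives 1.47, 1.73 and 2.02 at the three ICCs. A factor of 1.39 (2.776/1.994) comes from the t quantile alone. An analysis that uses the county pairs has 3 − 1 = 2 degrees of freedom and a critical value of 4.30. In the same simulation, the unpaired cluster-mean interval missed about 5% with no county variance, and the paired interval missed about 5% in every scenario.

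**The case against.** The strongest reply is that the document never says clustering will be ignored. Naming individuals as units of analysis also describes a mixed model fitted to individual data, so that sentence alone is no error. The form of the regression, the covariates and the small-sample correction are commonly left to a statistical analysis plan or full protocol, which are not shown. A reader might infer that the plan commits to an ordinary regression and unadjusted cost and QALY differences, so that every between-arm interval is bound to be too narrow. The text does not support this. The methods are unspecified, and the shortfall needs both an analysis that ignores clustering and positive variation within counties.

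A reader might also infer that false positive findings would decide whether a definitive trial goes ahead. The document does not say so. The Data analysis section plans description and intervals, no hypothesis test is set out, and the Abstract ties the definitive trial to feasibility and acceptability.

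These replies stand, and they limit the point and its severity. They do not remove it. The Sample size margins are stated numbers, and they reproduce only with a design effect of 1. The article also fixes the unit of analysis, gives Table 1 a column for statistical analysis, and reserves the ICC for the next trial. Followed as written, it leads an analyst to no allowance for clustering.

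**Conclusion.** The point holds in conditional form. The Sample size margins ignore clustering as stated. At ICC 0.01 to 0.10 with 10 per cluster, recruitment would be about ±12.9 to ±17.1 points, retention ±10.6 to ±14.0 and attendance ±12.6 to ±16.6, before any small-cluster correction. For the between-arm estimates no allowance is stated. Unless clustering is modelled, intervals will be too narrow for any positive between-cluster variation within county. The miss rate with 12 per cluster would be about 6%, 12% and 18% at ICC 0.01, 0.05 and 0.10, or about 5.5%, 8% and 11% with half the cluster variance between counties.

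These sizes rest on assumed ICCs, equal cluster sizes, normal outcomes and one ICC for both arms. The last may not hold, because control clusters receive usual care and share no sessions. The matter should be fixed, but is not critical, because the between-arm estimates are secondary and progression rests on feasibility.

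**What to change.** **Between-arm estimates.** In Randomisation, Table 1 and Data analysis, state that all between-arm estimates, costs and QALYs included, use a method that respects cluster and county and corrects for the small number of clusters. Two suitable choices are:
- a mixed model with county, a random cluster effect, the outcome's baseline value as covariate and a Kenward-Roger correction;
- baseline-adjusted cluster summaries with degrees of freedom that match the county pairing.

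If the resulting intervals are judged too wide to be useful, report each arm descriptively and give no between-arm confidence intervals.

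**Feasibility margins.** Restate the Sample size margins with an explicit design effect over a range of ICCs, as in the table above.

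**Optional.** Adjust QALYs for baseline EQ-5D-5L, which is already collected. This is a separate improvement and nothing in the article rules it out.

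**Cost.** Revised wording and a little more programming. No new data or participants are needed. The intervals become wider.
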